#### Recruitment

Patients are recruited at the four participating units. All clinicians at each unit are informed about the project and eligibility criteria and will help identify potential participants; the two LEAP therapists and/or dedicated research managers at the units are formally responsible for recruitment. Eligible patients will be informed about the study; advertisement material is also visible in waiting rooms and from clinicians. To reduce waiting time between recruitment and intervention start, participating units will identify as many potential participants as possible (ideally > 10 patients) prior to asking for participation interest. Upon interest, research contacts at each unit provide contact details to the PI or PC, who will then give oral or written study information to potential participants and provide the link for study consent and first assessment. Non-sensitive personal data (age, gender) for declining participants are collected. Pace of recruitment depends on patient influx on units. One group at a time per unit can be held with a maximum of two groups per semester. With a minimum of four participants per group, each unit could potentially include 16 LEAP participants per year. With four units, the participation goal would then be met within 12 months if equally many control participants are recruited. However, due to covid-19 restrictions, patient influx, and the randomization, a conservative time estimate for inclusion is 24 months (spring 2021 – summer 2023). Status of recruitment is monitored at least monthly with participating units through phone calls and/or e-mails.

#### Allocation

Each eligible patient consenting to participate will be assigned experimental condition using an online random number generator, stratified by site. An allocating investigator (AI) performs the randomization procedure and inform LEAP-therapists and participants. The AI is the only person with access to randomization group data.

#### Blinding

Participants and clinicians cannot be blind to group, since LEAP deviates too much from standard ED treatment. However, the PI will not have access to randomization group data until after the main treatment effects have been analyzed. Most assessments are self-report, but clinicians conducting diagnostic pre- and post-assessments are blinded. The LEAP therapists do not conduct assessments, neither do the PI or PC.

### Data collection and management

#### Outcomes

*Primary outcomes:* remission of ED diagnosis, improved ED psychopathology, and reduced pathological exercise behaviors and cognitions.

*Secondary outcomes:* normalized weight (BMI) and reduced general psychopathology.

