##### Primary research question

What are the treatment effects of LEAP on ED diagnosis, ED cognitions, CE behaviors and cognitions, BMI, emotion regulation and general psychopathology, after completion of the LEAP protocol.

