#### Sample size

Based on pilot data and power analysis with beta = .80, alpha = .05, effect size f = .25 and an estimated correlation between pre- and post-measures of .50, a total of 98 patients are required: 49 patients receiving LEAP and 49 controls. With an estimated drop-out rate of 30%, we will enroll 128 participants (64/arm). As there is a minimum of 4 participants in a LEAP group, length of time between initial assessment and first session of LEAP will vary for patients. This variation will need to be considered a covariate.

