#### Instruments/measures

##### Primary outcomes

Structured Eating Disorder Interview (SEDI [14];) is a semi-structured interview assessing ED diagnostic criteria according to DSM-IV. It is performed at T3; remission status (i.e., ED left or not) is used as outcome (binary data). The SEDI is also performed at three units at initial assessment to determine initial diagnosis. The SEDI has adequate psychometric properties [14]. The Eating Disorder Examination Questionnaire (EDE-Q [15];) is a 28-item questionnaire scored 0–6 (no days-all days) measuring severity of self-reported ED pathology the past 28 days. It generates an overall Global Scale and the subscales Restraint, Eating Concerns, Weight Concerns and Shape Concern. It also measures prevalence of ED behaviors such as restriction, binge-eating, purging and CE. This study will use information of presence and frequency of CE (binary and count data) and ED psychopathology scales as outcomes (continuous data). The EDE-Q has satisfactory psychometric properties [9, 16].The Compulsive Exercise Test (CET [17]; is a 24-item questionnaire scored 0–5 (never true-always true) measuring core psychological, behavioral, and emotional aspects of CE. It generates five subscales: Avoidance and rule-driven behavior, Weight control exercise, Mood improvement, Lack of exercise enjoyment, and Exercise rigidity. The LEAP treatment targets the aspects measured by the CET and all subscales are used as outcomes (continuous data). The CET has satisfactory psychometric properties [1, 17, 18].

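### Thirteen unranked variables hold primary status, while the sample size covers one unnamed continuous comparison at alpha .05

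*Protocol article*

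**What the plan says.** The Outcomes section of the protocol article lists the primary outcomes as "remission of ED diagnosis, improved ED psychopathology, and reduced pathological exercise behaviors and cognitions". No order is given among them.

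Under Instruments/measures, Primary outcomes, each domain becomes one or more variables:

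- SEDI at T3: "remission status (i.e., ED left or not) is used as outcome (binary data").
- EDE-Q: "It generates an overall Global Scale and the subscales Restraint, Eating Concerns, Weight Concerns and Shape Concern". The section continues: "This study will use information of presence and frequency of CE (binary and count data) and ED psychopathology scales as outcomes (continuous data").
- CET, which has five subscales: "The LEAP treatment targets the aspects measured by the CET and all subscales are used as outcomes (continuous data").

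The Statistical methods section gives every continuous outcome its own linear regression and uses logistic regression for categorical outcomes. Both are run per protocol and by intention to treat. The section mentions the primary outcome in the singular but does not say which variable that is.

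The Sample size section rests on a "power analysis with beta = .80, alpha = .05, effect size f = .25" and a pre-post correlation of .50, giving 98 patients, 49 per arm. It names no variable.

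The Primary research question is wider than the primary outcome list: "What are the treatment effects of LEAP on ED diagnosis, ED cognitions, CE behaviors and cognitions, BMI, emotion regulation and general psychopathology".

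**The concern.** A trial sized for one comparison at .05 should say which comparison that is. Here the sample size belongs to no particular variable, and a whole family of variables shares primary status. The article sets no order of testing, no requirement that all succeed, no split of alpha and no definition of a positive trial.

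Two things are at stake. If every variable is tested at .05, the chance of some primary result arising by chance is well above 5%. If the alpha is corrected later, the power stated in the protocol no longer applies. Either way, the reader of the results cannot tell in advance which test answers the question.

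**Working it through.** **1. Count of primary variables (Instruments/measures, Primary outcomes).** SEDI remission 1; EDE-Q Global plus four subscales 5; presence and frequency of compulsive exercise 2; CET subscales 5. Total 1 + 5 + 2 + 5 = 13.

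**2. The plan's own sample size.** Inputs from the Sample size section: f = .25, r = .50, alpha = .05, power .80 (printed as beta), two equal groups.

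- Baseline-adjusted comparison: noncentrality = f²N/(1 − r²) = .0625 × 98/.75 = 8.17.
- Between-group test on two measurements: f²N × 2/(1 + r) = .0625 × 98 × 2/1.5 = 8.17.

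With the noncentral F distribution, both give N = 98 as the smallest even total reaching .80, with power .808. The stated 98 is therefore reproduced, for **one** continuous comparison at .05. The calculation uses a standardised mean difference and a pre-post correlation. It does not describe remission, which is binary and which no entrant has at baseline.

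**3. Chance of at least one p < .05 among 13 with no true effect.** If independent: 1 − .95¹³ = 1 − .513 = .487. For results favouring LEAP only: 1 − .975¹³ = .280.

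The article gives no correlations between outcomes, so a range is assumed. Simulation of 13 equally correlated normal test statistics (200,000 draws) gives:

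| Assumed correlation | Any p < .05 | Favouring LEAP only |
|---|---|---|
| 0 (exact) | 49% | 28% |
| .3 | 42% | 21% |
| .5 | 33% | 17% |
| .7 | 24% | 12% |
| .9 | 14% | 7% |

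Correlations set by instrument were also tried: EDE-Q scales .7 to .85, CET subscales .3 to .5, the two compulsive-exercise variables .6 to .8, and .2 to .4 between blocks. These give 32% to 40% overall and 16% to 21% in LEAP's favour.

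**4. What a later correction would do.** The same power model with alpha divided by the number of tests:

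| Primary tests | Alpha per test | Power at N = 98 | N for power .80 |
|---|---|---|---|
| 1 | .05 | .81 | 98 |
| 3 | .0167 | .66 | 130 |
| 13 | .00385 | .46 | 172 |

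Power here is for any one continuous variable with f = .25.

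**5. Research question against outcome list.** The Primary research question includes BMI, emotion regulation and general psychopathology. The Outcomes section puts BMI and general psychopathology in the secondary tier. Instruments/measures, Secondary outcomes, lists the DERS, the emotion regulation measure, there as well. The two levels do not match.

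**The case against.** The strongest reply is that multiplicity procedures are commonly left to a statistical analysis plan, which is not shown here. That stands for the adjustment method, and the absence of one is not the point. Naming the primary outcomes and sizing the trial for them are done in this article, and a later correction over 13 tests would leave the trial short of power on its own assumptions (step 4).

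Several stronger readings are tempting but not supported:

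- **A chance positive is likely.** No scenario for the 13 tests reaches 50%. The 49% needs independence, which is implausible for scales from one questionnaire. Counting only results that favour LEAP halves the figures.
- **The plan tests each variable at .05.** This is inferred. The .05 appears only in the Sample size section, although no other threshold is given.
- **The count is exactly 13.** If the EDE-Q outcome were read as Global alone, there would be 1 + 1 + 2 + 5 = 9 variables and 1 − .95⁹ = 37% under independence. The conclusion is unchanged.
- **Two analysis sets make 26 chances.** Intention to treat is added because per protocol may overstate the effect. It checks the same hypotheses in largely the same patients.
- **Remission has some particular low power.** The article gives no remission rates. By the arcsine method at 49 per arm, with an assumed 30% in controls, power is about 18% against 40%, 53% against 50%, 72% against 55% and 86% against 60%. All that follows is that the stated calculation does not cover this outcome.
- **Emotion regulation has no assigned tier.** The Outcomes section does not mention it, but the DERS is listed under Secondary outcomes in Instruments/measures.

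**Conclusion.** The concern holds. The protocol fixes 13 unranked primary variables and a sample size for one unnamed continuous comparison. Tested at .05 each, the family-wise false-positive rate runs from 14% (correlation .9) to 49% (independence), with about one in three as a reasonable middle. In LEAP's favour it is 7% to 28%. These figures rest on the inferred per-test alpha and on assumed correlations. The other horn needs no correlation assumption: Bonferroni over 13 lowers power at 98 from .81 to .46. Bonferroni is conservative when outcomes are correlated, so a sharper method would lose less. The article does not provide for either route. The mismatch between the research question and the outcome tiers is a smaller wording fault.

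**What to change.** Before anyone sees outcome data by arm, name one continuous primary outcome to which the f = .25 calculation applies. EDE-Q Global would serve. So would a CET score, but the article describes only subscales, so the total and its scoring direction would have to be defined in advance. Alternatively, state a short fixed order, with other key outcomes such as SEDI remission tested at .05 only if the preceding test succeeds. Which outcome comes first is the sponsor's choice, since the Objectives name both pathological exercise and ED pathology.

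State the timepoint as well. The Statistical methods section uses T3 unless the program was completed before T2, so fixing T3 for the primary outcome would change that rule and should be done openly. Report the remaining subscales and the presence and frequency of compulsive exercise as secondary, with confidence intervals and no confirmatory claim. Align the Primary research question with the secondary status of BMI, emotion regulation and general psychopathology.

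The cost is wording in the protocol and the registry entry, with no added patients for this purpose: with one primary at .05, the 98 analysed patients stand. The downside is that fewer outcomes can carry a confirmatory claim. The Trial status section says recruitment had not begun. If it has since begun, the change stays credible while outcomes by arm are unseen, and the Blinding section already withholds allocation from the principal investigator until the main effects are analysed.

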#### Instruments/measures

##### Primary outcomes

Structured Eating Disorder Interview (SEDI [14];) is a semi-structured interview assessing ED diagnostic criteria according to DSM-IV. It is performed at T3; remission status (i.e., ED left or not) is used as outcome (binary data). The SEDI is also performed at three units at initial assessment to determine initial diagnosis. The SEDI has adequate psychometric properties [14]. The Eating Disorder Examination Questionnaire (EDE-Q [15];) is a 28-item questionnaire scored 0–6 (no days-all days) measuring severity of self-reported ED pathology the past 28 days. It generates an overall Global Scale and the subscales Restraint, Eating Concerns, Weight Concerns and Shape Concern. It also measures prevalence of ED behaviors such as restriction, binge-eating, purging and CE. This study will use information of presence and frequency of CE (binary and count data) and ED psychopathology scales as outcomes (continuous data). The EDE-Q has satisfactory psychometric properties [9, 16].The Compulsive Exercise Test (CET [17]; is a 24-item questionnaire scored 0–5 (never true-always true) measuring core psychological, behavioral, and emotional aspects of CE. It generates five subscales: Avoidance and rule-driven behavior, Weight control exercise, Mood improvement, Lack of exercise enjoyment, and Exercise rigidity. The LEAP treatment targets the aspects measured by the CET and all subscales are used as outcomes (continuous data). The CET has satisfactory psychometric properties [1, 17, 18].

##### Secondary outcomes

BMI (weight in kg / [height in m]^2^) is obtained at T1 and T3. At initial registration, some patients are weighed at units (mainly patients with AN), for others, height and weight are self-reported. At T3, BMI is self-reported through the SEDI interview. BMI at T3 is an outcome (continuous data).The Difficulties in Emotion Regulation Scale (DERS [19];) short-form (DERS-20) is a 16-item questionnaire rated 1–5 (never-always) measuring emotion dysregulation. The Total score is used in analyses (continuous data). DERS-16 has good psychometric properties [20, 21].The DSM-5 Self-Rated Level 1 Cross-Cutting Symptom Measure (DSM-5 symptoms [22]; measures presence and potential severity of general psychopathology in 13 symptom domains. Descriptive data for all domains will be presented and relevant domains may be used in analyses (binary and/or categorical data). The instrument has appropriate psychometric qualities [23].Feasibility and acceptance questionnaire, specifically designed for this study, measuring participants satisfaction with structure and content of LEAP (intervention group only; continuous data).

##### Additional measures

Eating Disorder Examination (EDE [24]) is an interview assessing ED pathology and diagnostic criteria according to DSM-5. One participating unit uses EDE to determine initial diagnosis. The concordance of the SEDI and EDE is high [14]. The EDE has good psychometric properties [25].The Active-Q [26] is a questionnaire measuring self-rated physical activity in daily life, both types of and time devoted to the specific activities (categorical and count data). Active Q is a valid and reproducible method for assessing physical activity [26].Treatment content questionnaire includes 4 items measuring content of TAU retrospectively and was specifically designed for this study. The questions ask about 1) the main focus of treatment, 2) if exercise has been targeted, if so, estimated percentage of treatment time devoted to exercise, 3) how exercise was targeted (if yes on item 2), and 4) if the respondent has changed his/her approach towards exercise, and if so, how (qualitative data).

#### Data collection methods (Table 2)

##### Data from medical journals

The project uses ED diagnosis from SEDI or EDE, BMI, and the EDE-Q rating as part of T1 data. If project inclusion takes longer than 3 months after initial assessment, these measures are reassessed at the units.

**Table 2 Tab2:** Schedule of LEAP enrolment, interventions, and assessments (SPIRIT figure)

			STUDY PERIOD			
		Enrolment	Pre-assessment	Allocation	Post-allocation	Close-out
TIMEPOINT	***-t***_***1***_	0	***t***_***1***_		***t***_***2***_	***t***_***3***_

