##### Self-report and interview data

The project includes three assessment timepoints when participants complete questionnaires: T1, 3-month (T2) and 6-month follow-up (T3). Apart from the medical record data at T1, all measurements are distributed to participants through BASS (see below) after study consent. T1 includes self-reports CET, DERS, DSM-5, and Active-Q; T2 includes all T1 self-reports plus the EDE-Q; T3 includes all T2 self-reports plus the treatment content questionnaire (all) and LEAP feasibility and acceptance questionnaire (intervention group only). At T3, the SEDI is also performed by phone.

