### Statistical methods

#### Outcomes (methods for analyzing primary and secondary outcomes)

To evaluate the LEAP treatment effect (primary objective) the data will be analysed per protocol and based on intention to treat. The first analysis will include all controls (TAU) and participants that complete the program (LEAP+TAU) and answer the questionnaires. The T3 assessment point will be used for post treatment data unless the participants completed the program before T2. Each continuous outcome measure will be used as a response variable in a linear regression model with group allocation and baseline value as predictors. Logistic regression will be used for categorical outcomes. Additional covariates in the models will include gender, clinic, and time between T1 and first treatment session. Since the removal of drop out and noncompliant subjects in the per protocol analysis may lead to overestimation of the treatment effect, we will also perform the same analysis on the basic of intention to treat. Here all subjects who were randomized to LEAP and answered the questionnaires will be included in the treatment group, independently whether they participated in the LEAP sessions. Assessment points with at least CET and EDE-Q will be included in analyses in relation to the primary outcome. If data is missing on CET and/or EDE-Q, the timepoint will not be considered for analysis. There will be no item level missing data (technically prohibited in BASS). The percentage of patients withdrawing from the program despite the initial intention to participate will be considered as a feasibility marker. To compare proportions of dropout and loss to follow-up within the groups, conventional two-sample Z-tests will be used. To identify prognostic factors associated with a good response to LEAP (secondary objective), the treatment group will be subjected to additional analysis where the outcome of interest is used as response variable in linear or logistic regression model and potential prognostic factors (e.g., BMI, type of ED) are used as predictors. These analyses will include all participants with complete data for each specific model.

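### The baseline EDE-Q is a clinic-record value up to 3 months old, not measured at T1, which may cost some precision on the EDE-Q outcomes

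*Protocol article*

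**What the plan says.** The Outcomes section of the protocol article makes ED psychopathology a primary outcome. The Instruments section takes it from the EDE-Q scales, which look back 28 days, and uses the same questionnaire for presence and frequency of compulsive exercise. Under Statistical methods, each continuous outcome is regressed on arm and its own baseline, with gender, clinic and the wait from T1 to the first session as further covariates.

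The section on data from medical journals counts the clinic's EDE-Q rating as T1 data and adds: "If project inclusion takes longer than 3 months after initial assessment, these measures are reassessed at the units". Table 2 agrees: the EDE-Q is marked at intake and has no mark at t1. So does the section on self-report and interview data: "T1 includes self-reports CET, DERS, DSM-5, and Active-Q; T2 includes all T1 self-reports plus the EDE-Q".

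Two data-handling statements bear on this value, both under Statistical methods: "There will be no item level missing data (technically prohibited in BASS", and "If data is missing on CET and/or EDE-Q, the timepoint will not be considered for analysis".

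The Sample size section uses "power analysis with beta = .80, alpha = .05, effect size f = .25" and "an estimated correlation between pre- and post-measures of .50", and concludes that "a total of 98 patients are required: 49 patients receiving LEAP and 49 controls".

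**The concern.** A baseline covariate earns its place through its correlation with the outcome. Here one primary instrument has a baseline of a different kind from the others. The CET is answered just before allocation, whereas the EDE-Q may have been answered weeks or months earlier. Patients must already be in outpatient care to be eligible, so symptoms may have moved under usual treatment in between. The age of the record differs from patient to patient, and no covariate represents it; the only timing covariate starts at T1.

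What is at stake is the precision of the EDE-Q comparisons. A weaker covariate leaves more residual variance and so lowers power for those outcomes. The record is made before allocation, so its error cannot depend on arm and no bias between arms follows. CET outcomes have their own T1 baseline and are touched only through the completeness rule.

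**Working it through.** **Timing.** A record at the 3-month limit (about 90 days) describes roughly days 118 to 90 before T1 (90 + 28 = 118). The month before T1 is days 28 to 0. The two windows stop overlapping once the record is more than 28 days old. T2 and T3 follow T1 by about 3 and 6 months, so the distance from EDE-Q baseline to outcome ranges from about 3 to 6 months at T2 (3 + 0 to 3 + 3) and from 6 to 9 months at T3 (6 + 0 to 6 + 3).

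**Reproducing the plan's 98.** Inputs from the Sample size section: alpha .05 (taken as two-sided), power .80 (the article labels it beta), f = .25, so d = 2f = .50 for two arms, and r = .50. For the planned regression on arm and baseline:

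- λ = d²·(N/4)/(1 − r²), noncentral F with 1 and N − 3 degrees of freedom.
- N = 98, r = .50: λ = .25 × 24.5/.75 = 6.125/.75 = 8.17, power 80.8%.
- N = 96 gives 79.9%, so 98 is the smallest even total that reaches 80%. The plan's figure is reproduced.

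**Varying r.** The documents give no correlation for an EDE-Q taken from intake records, so the range is assumed and runs to both sides of .50.

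| r (assumed) | 1 − r² | λ at N = 98 | Power at N = 98 | N for 80% |
|---|---|---|---|---|
| .60 | .64 | 9.57 | 86.5% | 84 |
| .50 | .75 | 8.17 | 80.8% | 98 |
| .40 | .84 | 7.29 | 76.2% | 108 |
| .30 | .91 | 6.73 | 72.8% | 118 |

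If the baseline carried no information (r = 0), λ = 6.125 and power is 68.8%. That is the floor.

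**A second formula also gives 98.** The article does not name its method. A repeated-measures ANOVA for the between-group effect with two measurements has λ = 2f²N/(1 + r), with N − 2 degrees of freedom. At N = 98 this is 12.25/(1 + r), again 8.17 at r = .50, with power 80.8%. The two agree there because 1 − r² = (1 + r)/2 = .75. Away from .50 they move in opposite directions: the second gives 83.4% at r = .40 and 86.0% at r = .30.

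**Data handling.** The claim of no missing items rests on a technical block in the online system. The section on self-report and interview data exempts the T1 record data from that system, and the Data management section has record data passed on by phone and entered in a separate dataset. The block therefore gives no assurance for the baseline EDE-Q. The completeness rule works on whole timepoints: read literally, a T1 without a record EDE-Q is dropped together with its completed CET. The same can happen at T2 or T3, because the online system saves each instrument as it is finished and a CET can exist without an EDE-Q.

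**The case against.** The documents are consistent with one another here, and the Participant retention section gives a reason for a short battery: to keep assessments brief. The reassessment rule limits how old the record can be. The correlation of .50 is said to rest on pilot data, is tied to no outcome or time lag, and may already allow for an intake baseline. All of this stands, and it is why the loss cannot be sized from the documents.

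Some stronger readings are tempting but not supported:

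- *Pooling candidates makes very old baselines likely.* The Recruitment section says that "participating units will identify as many potential participants as possible (ideally > 10 patients) prior to asking for participation interest". But candidates may come from the existing caseload, and a wait beyond 3 months triggers a new assessment. Pooling can move records towards the limit, not past it.
- *The sample size depends on this adjustment.* The formula is not named, and one of the two that give 98 gains power as r falls. The loss shown above applies to the regression that the plan will run, not necessarily to the calculation behind 98.
- *Some participants may no longer exercise compulsively at randomisation, so the entry criterion fails.* Eligibility asks for compulsive exercise at initial assessment, so this is no departure from the plan. The remedy below would not change it either.
- *Participants will be lost because records are missing.* Table 2 makes the EDE-Q standard at intake, and nothing suggests that it will often be absent.
- *The statement on missing items is false.* It is tied to the online system. For the record value it is unsupported, not shown to be wrong.

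**Conclusion.** The point holds as a modest design weakness confined to the EDE-Q outcomes. Their baseline is not concurrent with T1, its age varies up to 3 months, and the gap is not modelled. The expected harm is lost precision, not bias between arms.

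The size is unknown. Under the planned regression with 98 analysed, falling from r = .50 to .40 costs 4.6 percentage points of power (80.8 − 76.2), and falling to .30 costs 8.0 (80.8 − 72.8). If r is .60 despite the record's age, power is 86.5% and there is no shortfall. These figures assume a two-sided test, d = .50 and equal arms of 49; the drop in r is itself an assumption.

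Separately, the completeness rule as worded can remove usable CET data for a reason unrelated to the CET, and the safeguard against missing items does not extend to the record EDE-Q. How often either would matter cannot be judged from the article.

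**What to change.** 1. Add the EDE-Q to the T1 online battery, completed with the CET before allocation, and use that value as the baseline for all EDE-Q outcomes. Keep the record value as a fallback when the T1 EDE-Q is missing, with its date noted. Eligibility can continue to rest on the intake assessment.
2. Apply the completeness rule outcome by outcome, so that a missing EDE-Q never removes a CET value and a missing CET never removes an EDE-Q value.
3. Limit the statement on missing items to instruments collected through the online system.

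The cost is one 28-item questionnaire, already delivered online at T2 and T3, and a few minutes of participant time at T1. That runs slightly against the aim of a short battery. The other two changes are wording only. The Trial status section reports that recruitment had not begun, so at that stage the change would apply to every participant.
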